### Secondary study parameters and analysis

Although this is a phase 2 trial, we will also register secondary outcome parameters such as (progression-free) survival and quality of life as they are also aspects of safety. The incidence of advanced stage cervical cancer is quite low in the Netherlands. Including these secondary parameters will make it possible to enter these patients into a subsequent phase 3 trial, if the current PALDISC study shows that such a phase 3 study is indeed necessary. Decision on the necessity of a phase 3 trial will depend on whether surgical staging of PALN in advanced stage cervical cancer is deemed safe, feasible and necessary in comparison with the performance of current PET-CT imaging.

The proportion of changed initial treatment plans and diameter of metastases will be documented and presented. Data on sensitivity, specificity and negative and positive predictive values of MRI, PET-CT and surgical staging will be documented in 2 × 2 tables; estimates will be provided with 95% CI.

Time to treatment will be measured in days from the day of randomization until start of chemo radiation. Difference in treatment delay between the arms, due to surgical intervention and histological analyses, will be presented using a Kaplan-Meier curve with the corresponding medians and 95% CI. Rate differences and 95% CI for mortality and morbidity during follow-up will be calculated and presented in a table.

The analysis of progression-free survival and overall survival will be based on and presented in a Kaplan-Meier curve with corresponding hazard ratio and 95% CI. Means and range in reported quality of life will be reported using the Dutch versions of the European Organisation for Research and Treatment of Cancer (EORTC) Core Questionnaire, the QLQ-C30 version 3.0 and the supplemental cervical cancer-specific module, the QLQ-CX24 [24, 25]. The difference in quality of life between the arms will be presented as a mean difference with 95% CI.

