**Methods/design:**

In addition to standard imaging (MRI or CT scan) with PET-CT, 30 adult women with FIGO stage IB2, IIA2–IVA cervical cancer will be randomised to receive either surgical staging or usual PET-CT staging. Administering extended field radiotherapy will be based on lymphadenectomy results for the intervention group and on the PET-CT results for the control group. Follow-up visits at 0, 3, 6, 9 and 12 months will assess health-related quality of life and progression-free survival.

Primary safety and feasibility outcomes of surgical staging will be assessed by calculating means with 95% confidence intervals for duration of surgery, number of complications, blood loss, nodal yield after para-aortic lymphadenectomy and treatment delay due to surgical staging. Secondary patient-centred outcomes on quality of life and first year survival will be documented and compared between the two groups. Estimates of sensitivity, specificity and negative and positive predictive values of MRI, PET-CT and surgical staging will be presented with 95% CI.. All analysis will be performed according to the intention to treat principle.

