### Inclusion criteria

Women (aged ≥ 18 years) with FIGO IB2, IIA2, IIB, IIIA, IIIB and IVA cervical cancer from general and specialised hospitals for gynaecologic care in the Netherlands are eligible for randomization after meeting the following criteria:Age of 18 years or above;Histologically confirmed squamous cell, adenosquamous or adenocarcinoma of the cervix;FIGO stage IB2, IIA2, IIB, IIIA, IIIB and IVA, staging performed by examination under anaesthesia;Fit for surgery;WHO-performance 0-2;WBC > 3.0 × 109/L, platelets > 100 × 109/L, creatinine clearance > 60 ml/min;Chest CT or X-ray, abdominal MRI or CT scan and PET-CT with no evidence of distant metastasis (PET positive > 2 cm);Written informed consent.

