**Fig. 2 Fig2:**
[figure not shown]
Patient flow

Histological analysis of PALN will be performed node by node and includes all normal procedures with an additional assessment on lymph node yield, node diameter and diameter of micro metastases. Patients with metastatic PALN on histological analysis will receive extended field radiation therapy with concurrent chemotherapy and optional adjuvant chemotherapy. To ensure a comprehensive assessment of the primary tumour, nodal sites and potential metastatic sites, a physical examination including a rectovaginal examination under anaesthesia and radiology including a chest CT or X-ray, abdominal MRI and PET-CT scan are performed. All PET-CT-detected para-aortic lymph nodes will be described and registered per region. In the surgical staging group, all PALNs will be excised, described and registered per region in order to correlate radiological, surgical and histological findings.

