### Control group

Patients in the control group will receive treatment according to the current guidelines, i.e. treatment with regards to PALN status will be based on PET-CT.

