## Discussion

The PALDISC trial will assess safety and feasibility of surgical staging in patients with locally advanced cervical cancer in the Netherlands. It will provide insight in diagnostic accuracy of the PET-CT and detection rate of missed (micro)metastases due to surgical staging.

So far, all available evidence regarding the validity and diagnostic accuracy of PET-CT in detecting PALN metastases in locally advanced cervical cancer is based on a study with 16 patients only [10]. This leads to a high uncertainty regarding both sensitivity and specificity, which is represented by the large confidence intervals. As a result, patients may have a high chance on false negative and/or false positive PET-CT results, leading to subsequent under- and overtreatment, respectively. Undertreatment may lead to a deterioration of overall and progression-free survival, while overtreatment may lead to unnecessary radiation. Both have detrimental effects on the quality of life of patients as well as hospital and health care expenses.

To compare the effectiveness and diagnostic accuracy of a PET-CT with surgical staging, a phase 3 randomised controlled trial is the most warranted design. However, as para-aortic lymphadenectomy is not standard of care for cervical cancer patients in the Netherlands, we feel the need to first assess its safety and feasibility.

A major strength of our study is that safety and feasibility of the para-aortic lymphadenectomy is assessed on both subjective (quality of life) and objective (time of treatment delay, blood loss, adverse events, etc.) outcome measures. In addition, data on both sensitivity and specificity should also be considered. Although this study only includes 15 patients, it is almost a doubling of the currently available number of patients in whom PET-CT was compared to gold standard histology (*n* = 16) [10]. Furthermore, these outcomes can be compared to current standard of care while controlling for confounders and selection bias due to the randomization. These strengths will provide vital information for a group of experts in order to make the final decision whether or not a phase 3 trial is deemed safe and necessary.

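### Sensitivity, specificity and predictive values are promised for surgical staging, but the only reference standard is its own histology, so all four are 100% by construction

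*Protocol article*

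**What the plan says.** Secondary study parameters and analysis states: "Data on sensitivity, specificity and negative and positive predictive values of MRI, PET-CT and surgical staging will be documented" in 2 × 2 tables, with 95% CIs. The Abstract makes the same promise: "Estimates of sensitivity, specificity and negative and positive predictive values of MRI, PET-CT and surgical staging will be presented with 95% CI". Surgical staging is thus listed as a third index test beside the two imaging tests.

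The reference standard has to be gathered from other sections. Background, Discussion and Trial status all treat histology of the para-aortic nodes as the gold standard; the Discussion counts the patients "in whom PET-CT was compared to gold standard histology". Background describes surgical staging as para-aortic lymphadenectomy that makes histological evaluation of the nodes possible. The section on intervention, surgical procedure and histological analysis has treatment in that arm follow the histological result.

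Only the surgical arm has nodes excised. For controls, "treatment with regards to PALN status will be based on PET-CT". The general analysis rule in the Abstract is: "All analysis will be performed according to the intention to treat principle". The section on data entry and missing data repeats intention to treat for all data and prescribes multiple imputation where data are assumed missing at random.

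On MRI, the Inclusion criteria require "abdominal MRI or CT scan and PET-CT with no evidence of distant metastasis", whereas the intervention section says "abdominal MRI and PET-CT scan are performed".

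**The concern.** A 2 × 2 accuracy table needs an index test and a separate reference. For PET-CT and MRI the reference is para-aortic histology. For surgical staging, no reference other than that same histology is named, so the table has no information to offer.

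What is at stake is interpretation. The section on secondary parameters ties the case for a phase 3 trial partly to whether surgical staging is necessary given how PET-CT performs. A table showing surgical staging at 100% with a confidence interval, next to an imperfect PET-CT, would look like a head-to-head result. The contrast would come from the definitions alone.

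A smaller point follows. The article does not say which patients enter the PET-CT and MRI tables, while its general rules refer to all data and to imputation.

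**Working it through.** **Inputs.** 15 patients per arm (section on sample size). Para-aortic metastasis prevalence of about 20%, with other studies up to 40% (Background). Earlier PET-CT accuracy against histology in 16 patients: sensitivity 50% (7–93%), specificity 83% (52–98%) (Background). I assume that all 15 surgical-arm patients are operated on and have evaluable nodes.

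**Step 1: reproduce the plan's own figure.** The exact (Clopper-Pearson) 95% interval for x successes in n has lower limit Beta(0.025; x, n − x + 1) and upper limit Beta(0.975; x + 1, n − x), both as quantiles.
- 2/4 = 50%: 6.8–93.2%, matching 7–93%.
- 10/12 = 83.3%: 51.6–97.9%, matching 52–98%.
- 4 + 12 = 16, the stated size. These are the only splits with denominators up to 15 that match.

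The cited figures are therefore exact binomial intervals, and I use the same method below.

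**Step 2: surgical staging against its own histology.** Let T be the surgical-staging result and R the reference. Both are the histology of the same nodes, so T = R in every patient and false positives = false negatives = 0. With P node-positive and N node-negative patients:
- sensitivity = P/P and PPV = P/P;
- specificity = N/N and NPV = N/N.

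All equal 100%. Sensitivity and PPV are undefined if P = 0; with 15 patients the chance of that is 0.8^15 = 3.5% at 20% prevalence and 0.6^15 = 0.05% at 40%.

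**Step 3: the intervals that would be printed.** For x = n the lower limit reduces to 0.025^(1/n) and the upper limit is 100%.

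| Prevalence | Positive / negative | Sensitivity and PPV | Specificity and NPV |
|---|---|---|---|
| 20% | 15 × 0.2 = 3 / 12 | 0.025^(1/3): 29–100% | 0.025^(1/12): 74–100% |
| 40% | 15 × 0.4 = 6 / 9 | 0.025^(1/6): 54–100% | 0.025^(1/9): 66–100% |

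Each limit is a function of n only. No observation in the trial could change it, apart from how many patients turn out node-positive.

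**Step 4: what the design can estimate.** PET-CT against histology in the same 15 patients:
- Sensitivity near 50%: 1/3 gives 1–91% and 2/3 gives 9–99% (20% prevalence); 3/6 gives 12–88% (40%).
- Specificity near 83%: 10/12 gives 52–98% (20%); 7/9 gives 40–97% (40%).

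These are wide but real estimates, because PET-CT and histology can disagree.

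**The case against.** **A surgical judgement could be the index test.** The intervention section speaks of correlating imaging, surgical and histological findings, so a macroscopic assessment at operation might be meant. That would remove the circularity. However, no such assessment is defined, and treatment follows histology. The objection shows one way to repair the plan; it does not show that the plan is sound as written.

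**Half the randomised patients have no reference standard.** A reader might infer that this invalidates the accuracy results. The documents do not support that. The Discussion openly counts 15 patients for the PET-CT comparison, and excision is limited to the surgical arm. Because allocation is randomised, absent control histology costs precision and does not in itself cause verification bias, provided the tables use operated patients only.

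**Imputed histology in controls.** A reader might also take the intention-to-treat and imputation statements to mean this. The article proposes no such thing. Control histology is never scheduled, so it is not missing in the ordinary sense, and an article may leave the analysis set to the full protocol. What stands is that the general statements carry no exception, and one sentence would settle it.

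**MRI not paired with PET-CT.** This reading fails. PET-CT is required of every eligible patient, so anyone with an MRI has both scans, and the intervention section says MRI is performed. What remains is a mismatch between MRI-or-CT and MRI.

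**Effect on the phase 3 decision.** No threshold uses the accuracy of surgical staging. The criterion refers to PET-CT performance, which can be estimated, and the decision rests with a group of experts. This is a fair reason to moderate the severity.

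**Conclusion.** The point holds for surgical staging. As defined in the article, its sensitivity, specificity, PPV and NPV against the only named reference are fixed at 100%, and the promised intervals would carry no information about accuracy. The size of those intervals rests on 15 operated patients with evaluable nodes and on prevalence of 20–40%; the circularity itself rests on neither.

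The PET-CT and MRI tables are valid in principle and need only an explicit analysis set. This should be fixed, but it is not critical: it concerns a descriptive secondary output with no test or threshold attached, and the primary outcomes are unaffected. Trial status reports that the trial was cancelled after five enrolments. The correction still matters because the article is published in the hope that other centres will take up such a trial.

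**What to change.** 1. In the Abstract and in Secondary study parameters and analysis, delete surgical staging from the tests for which accuracy is estimated. Alternatively, define it separately from the histology and name an independent reference.
2. State that the PET-CT and MRI 2 × 2 tables use only surgical-arm patients with para-aortic histology, as an exception to the general intention-to-treat and multiple-imputation statements, with exact 95% CIs.
3. Split the already planned proportion of changed treatment plans into PET-negative/histology-positive and PET-positive/histology-negative. These counts address directly what surgical staging adds to PET-CT.
4. Reconcile MRI or CT (Abstract, Inclusion criteria) with MRI (intervention section), and compare MRI with PET-CT in operated patients who had both.

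The cost is wording; deleting the index test and restricting the tables add no patients or procedures. The downside is that one advertised set of estimates disappears.

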### Randomisation, blinding and treatment allocation

After providing informed consent, all patients will be randomised by the enrolling clinician using the randomization program provided by Castor EDC. Patients will be randomised equally between surgical staging and standard treatment using a permuted block design per centre; the allocation sequence itself is concealed from the patient, investigator and clinician [19]. Blinding of the patient, investigator and/or observer from the allocation result is not possible.

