### Sample size calculation, data monitoring and premature termination of the study

We will include 15 patients in each arm for this phase II study. There will be no formal data-safety monitoring board due to the relatively small number of patients (*n* = 15) in the intervention arm. However, due to the nature of this intervention and possible risk related to the intervention, we have installed an independent expert to ensure the safety and ethics. After each serious adverse event, which may in any way be related to the para-aortic lymphadenectomy, all inclusions and planned interventions at all centres will be stopped immediately. All principle investigators will converge and decide whether it is ethical to resume inclusion after the serious adverse event has abated or until a stable situation has been reached. All meetings and decisions will be documented. Each conclusion will be submitted to the independent expert for an independent assessment on safety and ethics. The trial will only resume after both the principle investigators and independent expert agree that safety and ethical criteria are being met. An independent monitor will check all centres on informed consent, adherence to the in- and exclusion criteria, reporting of all adverse events and full source document verification. The monitor will audit after the first three included patients and then yearly or after every 10 included patients.

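### The quality-of-life difference is given as a mean difference with no stated adjustment for month-0 score or centre; if unadjusted it is valid, but probably less precise than the data allow

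*Protocol article*

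**What the plan says.** The section on secondary study parameters first promises means and range for the two EORTC questionnaires and then says: "The difference in quality of life between the arms will be presented as a mean difference with 95% CI". It names no covariate, model or time point.

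Three other statements bear on this:

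- **Timing** (Abstract, Methods/design): "Follow-up visits at 0, 3, 6, 9 and 12 months will assess health-related quality of life and progression-free survival". Month 0 is listed among the follow-up visits, and the text gives no event from which the months are counted.
- **Allocation** (Randomisation, blinding and treatment allocation): "Patients will be randomised equally between surgical staging and standard treatment using a permuted block design per centre".
- **Size** (Sample size calculation): "We will include 15 patients in each arm for this phase II study".

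The role of the outcome is explained in the secondary parameters section: "we will also register secondary outcome parameters such as (progression-free) survival and quality of life as they are also aspects of safety". The Discussion counts quality of life as part of a major strength of the study.

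**The concern.** The natural reading is a simple difference between arm means. Two pieces of design information would then go unused: the month-0 score and the centre used to block the randomisation. In a large trial this matters little. With 15 per arm, chance differences between the groups at the start are sizeable, and a simple difference carries part of any such difference into the estimate. What is at stake is precision, and protection against a chance imbalance, in an outcome that the article treats as an aspect of safety.

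The month-0 score can serve as a covariate only if it is recorded before the intervention can affect it. The article does give an origin for time to treatment (the day of randomisation) but none for the quality-of-life visits.

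**Working it through.** **No figure in the plan to reproduce.** The article states no quality-of-life SD, correlation, precision target or power, and gives 15 per arm without derivation.

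**Inputs from the article:** 15 per arm, 95% CI, 1:1 blocked allocation per centre, two named centres. **Assumed:** the correlation *r* between month-0 and follow-up scores, varied from 0 to 0.7; equal SDs at both times; no centre effect. Results are in SD units, so no SD has to be assumed.

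**1. Unadjusted interval.** Half-width = t(0.975; 28 df) × √(2/15) = 2.048 × 0.365 = 0.748 SD.

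**2. Chance baseline imbalance.** The standard error of the month-0 difference is √(2/15) = 0.365 SD. The probability of an imbalance above 0.5 SD in either direction is P(|Z| > 0.5/0.365) = P(|Z| > 1.37), about 17% for any one scale. This needs no value of *r*. Given a 0.5 SD imbalance, the unadjusted estimate is shifted on average by *r* × 0.5 SD, which is 0.25 to 0.35 SD for *r* = 0.5 to 0.7.

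**3. Gain from adjustment.** In large samples, variance is multiplied by 1 − *r*². At this size the model pays for estimating its coefficients and drops from 28 to 26 residual df. The last two columns come from 15,000 simulated trials of 15 v 15 in two near-equal centres. They compare the unadjusted t interval with ANCOVA on month-0 score and centre.

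| *r* (assumed) | Large-sample variance reduction, *r*² | Simulated variance change | Simulated mean CI width change |
|---|---|---|---|
| 0 | 0% | 4.2% larger | 2.4% wider |
| 0.3 | 9% | 4.9% smaller | 2.3% narrower |
| 0.5 | 25% | 22.0% smaller | 11.3% narrower |
| 0.7 | 49% | 46.4% smaller | 26.8% narrower |

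The half-width of 0.748 SD becomes about 0.748 × (1 − 0.113) = 0.66 SD at *r* = 0.5 and 0.748 × (1 − 0.268) = 0.55 SD at *r* = 0.7.

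**4. Source of the gain.** All of it comes from the month-0 score. With blocks balanced within centre and no centre effect, the centre term adds nothing. The reason to include it is that the analysis should reflect the stratified randomisation.

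**5. Effect on power.** For an illustrative 0.5 SD difference, approximate power is Φ(0.5/(0.365√(1 − *r*²)) − 1.96): 28% at *r* = 0, 35% at 0.5 and 48% at 0.7. These use the large-sample variance and so slightly flatter the adjusted analysis.

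**The case against.** The strongest objection is that the article never calls the difference raw or unadjusted. An ANCOVA or mixed-model estimate is also a mean difference with a 95% CI, and an article commonly leaves covariates to the full protocol or SAP, which are not shown. This stands to the extent that one cannot say the plan has chosen an unadjusted analysis. It does not remove the point: the article names an estimator directly after simple descriptives, and its Discussion mentions no control of confounding other than randomisation. Naming the adjustment improves the method as stated.

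It is also fair that an unadjusted randomised comparison is unbiased and that its interval already allows for chance imbalance. A reader might infer that the planned comparison is invalid; it is not.

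A reader might also take a loss of a quarter to a half of the precision as established. Those figures are *r*² for *r* of about 0.5 to 0.7, apply to variance in large samples, and rest on a correlation found nowhere in the documents. Nor is it shown that one correlation would hold from month 3 to month 12.

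Finally, a reader might infer that month 0 falls after surgery, leaving no true baseline. The text does not say so, and the SPIRIT and patient-flow figures, which may settle it, are not available. What stands is that the text gives no origin, and that any gain from adjustment depends on a pre-surgery month 0.

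The practical weight is small. The outcome is secondary, no test or precision target is attached to it, and the Trial status section reports cancellation after five patients with one active centre.

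**Conclusion.** The point holds as a modest recommendation on analysis. The article states no adjustment of the quality-of-life difference for month-0 score or centre. If the difference is unadjusted, it is valid but probably less precise than the collected data allow. Under an assumed correlation of 0.5 to 0.7, adjustment saves about 22% to 46% of variance and 11% to 27% of CI width at 15 per arm. The benefit is negligible at 0.3 and becomes a slight loss at 0. Even in the favourable range, power for a 0.5 SD difference stays below one half, so adjustment sharpens the estimate without making the comparison well powered. With recruitment stopped at five patients, the point matters mainly for any centre that takes up the design and for the article's idea of carrying these patients into a phase 3 trial.

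**What to change.** State that QLQ-C30 and QLQ-CX24 scores will be analysed by ANCOVA at each visit, or by a mixed model for repeated measures, with month-0 score and centre as covariates. Report the adjusted mean difference with its 95% CI. State also that the month-0 questionnaire is completed at randomisation before any surgery, and that months 3 to 12 are counted from randomisation in both arms.

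The cost is a sentence on analysis and one on timing, with no extra visits. Statistically it uses one degree of freedom for month-0 score and one for centre (two centres), with a slight loss of precision if the correlation is near zero. If only one centre contributes patients, the centre term drops out.
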